### Ethics and dissemination

#### Ethics approvals

The research protocol (version 1.2 dated January 2018) for this study has been approved by the Scientific and Ethics Review Unit (SERU) at Kenya Medical Research Institute (KEMRI), Nairobi (on 12 March 2018, Ref. SERU# 3507). The trial is registered with the Pan-African Clinical Trials Registry, PACTR202001919442161. The trial is conducted in compliance with the Declaration of Helsinki and the ICH Good Clinical Practice (GCP) guidelines. Approvals for changes to the protocol (for example, amendments) will be sought from the ethics committee, and the approved changes communicated to the study team and participants.

#### Study and data monitoring

The principal investigator and the study investigators oversee the implementation of the study, including adherence to the protocol, participant recruitment, retention and follow-up, administration of the study drugs and compliance monitoring, and quality of the accruing data. Partly due to the established safety profile of the study drugs, and the duration of the study we have not established a data safety monitoring board and interim analysis is not planned.

#### Consenting process

A meeting was held with parents, teachers, and community leaders to inform them about the study’s aims, procedures, potential benefits, and risks. Permission to conduct the study is obtained from the Kirinyaga County Commissioner, the Kirinyaga County Directorates of Health and Education, and the respective school administration. School children in grades 3 to 5, aged between 9 and 15 years old, are informed about the study and asked to provide a stool sample to be tested for *S. mansoni*. Children and parents/guardians of all children who test positive for *S. mansoni* are invited to a meeting where general information about schistosomiasis, the aims of the study, procedures, potential risks, and benefits are explained in the local languages (Swahili and Kikuyu) and in a culturally sensitive way. The study nurse obtains written informed consent from the parents/guardians and verbal assent from the child. All the study personnel are trained in GCP. We explain that no biological samples are stored for any ancillary studies. A copy of the child assent and parental informed consent used in the study is provided in an online supplemental file (Additional file 1: Appendices 1–3).

#### Withdrawal

Participation is voluntary, and participants can withdraw from the study at any time and for any reason without consequences. Participants will be withdrawn from the study due to repeated vomiting or occurrence of SAE. Children with SAEs are followed up until the end of 6 weeks after the last treatment dose. Participants withdrawn from the study due to medical reasons are referred to adequate health facilities for further care. Unless consent is withdrawn, efforts are made to assess these children at the week 6 follow-up schedule.

Valid reasons for study discontinuation include completion of the scheduled follow-up period and exclusion from follow-up. Randomized participants who miss one or more scheduled follow-up visits remain in the study and are followed up as planned. Loss to follow-up is expected to be minimal because all the participant-related study procedures are completed at school and, if necessary, at home. In the unlikely event that a study participant moves away from the study area during the study period, they are considered lost to follow-up and are not included in the efficacy analysis. However, data collected up to the time of withdrawal will remain in the study and be used for analysis of whether or not the participant continues with the follow-up visits. Participants who have been withdrawn from the study are administered a standard dose of praziquantel after the final study visit. No additional participants are recruited to replace those who have withdrawn.

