### Criteria for withdrawal or discontinuation from the study

The objective criteria for discontinuation from study medication and/or institution of another form of treatment include the following:Parent/guardian’s withdrawal of consentDevelopment of a concomitant illness that would interfere with the clear interpretation of study outcomesInability to retain study medication due to vomitingAny serious adverse event requiring treatment withdrawal in the opinion of the study clinician or at the request of a parent/guardianMajor protocol violation, omission of more than one treatment dose, or a credible report of self-medication with an additional anti-schistosomal or antimalarial drug outside the study protocol

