### Adverse events

The study nurse administers all the study drugs. Children will ingest the study drugs with a small amount of water. Before administering the study treatment, all the children are given a light meal (slices of bread and a glass of orange juice) to reduce the study drugs’ nauseating effect and improve drug bioavailability [32]. Participants are observed for 1 h after drug ingestion to ensure retention and to assess for any immediate adverse events. Participants who vomit within 1 h of drug ingestion are re-dosed. Participants with repeated vomiting are withdrawn from the study.

All adverse events are elicited by asking the children about any adverse drug reactions observed after taking the study drugs. The symptoms will be assessed, graded (according to their intensity as perceived by the child) by the study clinician, and recorded on the adverse event form. The adverse events form is administered an hour after study treatment and 24 h later (before the next ACT dose). The following information is recorded on the adverse events form: adverse event description, duration (start and end dates); severity grade (mild, moderate, severe); causality (relationship to the study drugs); action(s) taken; and the outcome. The participants who develop adverse events (AEs) or serious adverse events (SAEs) are treated appropriately and followed up until they return to a normal state of health. The investigator reports any SAE occurring or observed during the follow-up period to the KEMRI Scientific and Ethics Review Unit within 48 h of being aware of the event.

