### Data management and analysis

Data collected from each participant is recorded on paper-based case report forms (CRFs) in black ballpoint pen. The principal investigator will ensure that the data in the CRFs are accurate, complete, and legible. Data from the case record forms is entered by a data clerk into computers as they accrue using the MS Access program. The data is verified by comparing it with the CRFs. Missing data is imputed as either treatment success or treatment failure (assuming the same infection intensities before and after treatment). Validated data is transferred to SPSS version 20 and STATA version 12 for statistical analyses. The CRFs and the electronic data will be kept for 5 years after the primary manuscripts are published.

Data is analyzed using SPSS for Windows version 20 (SPSS Inc., Chicago, IL) and STATA version 12.0 (StataCorp., College Station, TX, USA) packages. A two-sided *p*-value less than 0.05 is considered statistically significant for all tests.

Demographic and other baseline characteristics are compared to check for imbalances between the study groups. These measures will be tabulated from the intent-to-treat population. Significance tests are not performed to compare the differences between study groups at baseline. Where imbalances are suspected, additional analyses are performed to adjust for these variables.

To determine efficacy, both the per-protocol and intention-to-treat analyses are done, but the per-protocol analysis is the main approach. The primary efficacy outcome is the cure rate, defined as the proportion of children infected with *S. mansoni* at enrollment but not excreting eggs by week 6 after taking the study treatment. In the computation of the cure rate, children randomized to the PZQ alone study arm are considered the control group. Cure rates are compared between the treatment groups using Pearson’s chi-square test for contingency tables (in a per-protocol analysis) and summarized as absolute risk differences with 95% confidence intervals (CI). The per-protocol population is defined to include all participants who were randomized and who completed the study procedures to week 6 or 12. The primary hypothesis for non-inferiority is assessed by considering the lower limit of the 95% CI for the risk difference. Non-inferiority is concluded if the lower bound of the 95%CI from the risk difference does not exceed the non-inferiority margin of − 10.

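### Two sections set different end points for following a serious adverse event, and the Withdrawal section removes any child who has one, with assessment sought only at week 6 (minor)

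*Protocol article*

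**What the plan says.** **End of SAE follow-up.** The Adverse events section covers non-serious and serious events in one sentence: affected children "are treated appropriately and followed up until they return to a normal state of health". The Withdrawal section sets a calendar limit for the serious ones: "Children with SAEs are followed up until the end of 6 weeks after the last treatment dose".

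**Effect of an SAE on participation.** The Withdrawal section says: "Participants will be withdrawn from the study due to repeated vomiting or occurrence of SAE". It attaches no condition about severity, causality or remaining doses. The earlier section headed Criteria for withdrawal or discontinuation from the study introduces its list as "The objective criteria for discontinuation from study medication and/or institution of another form of treatment". The SAE item in that list is limited to an event that calls for stopping treatment, as judged by the clinician or asked for by a parent or guardian.

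**After withdrawal.** For children withdrawn for medical reasons who have not withdrawn consent, "efforts are made to assess these children at the week 6 follow-up schedule". No equivalent sentence covers week 12. The same section adds: "Participants who have been withdrawn from the study are administered a standard dose of praziquantel after the final study visit", and that "data collected up to the time of withdrawal will remain in the study".

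**Analysis.** Under Data management and analysis, "both the per-protocol and intention-to-treat analyses are done, but the per-protocol analysis is the main approach".

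**The concern.** One follow-up rule ends on a clinical state and the other on a date. For a child whose SAE is still open at the date limit, staff cannot apply both. Read literally, a non-serious event could be followed longer than a serious one. The participants are children aged 9 to 15, and no data safety monitoring board has been set up (Study and data monitoring), so the written SAE rules carry more of the protection.

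The withdrawal rule raises a different problem. Dosing ends on D0 in the control arm and D2 in the combination arms (Table 1). A child with a later SAE has no dose left to stop, yet the Withdrawal section still takes that child out of the study. Stopping a drug and leaving the study are treated as one step. The possible losses are the recorded outcome of the SAE and the week-12 stool result, which feeds the cumulative cure rate, the egg reduction rate and the re-infection outcome.

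**Working it through.** The plan has no figure of its own to reproduce here. The check compares the text and then sizes the consequence.

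**1. The date limit by arm.** Inputs: last dose on D0 (control) or D2 (combination arms), from Table 1; 6 weeks = 42 days.
- Control: 0 + 42 = day 42.
- Combination arms: 2 + 42 = day 44.

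**2. Follow-up allowed for an SAE starting on day d.** The Withdrawal rule gives 42 − d days (control) or 44 − d days (combination). The Adverse events rule gives no limit.

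| SAE onset | Control | Combination arms | Adverse events section |
|---|---|---|---|
| Day 28 | 14 days | 16 days | until recovered |
| Day 42 (week-6 visit) | 0 days | 2 days | until recovered |

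The rules diverge for any SAE still open at day 42 or 44. An SAE that begins after the limit is not counted here as a conflict, because only the Adverse events rule can then apply.

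**3. Could the date be a minimum?** The sentence gives an end point and nothing marks it as a minimum. Table 1 marks adverse events up to week 6 and not at week 12. The week-12 visit does include a brief history and examination, but the only explicit rule that carries an open SAE past week 6 is the one in the Adverse events section.

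**4. The two withdrawal statements.** The heading of the criteria section refers to the study, while its lead-in refers to study medication and its list is not presented as complete. If the section governs study withdrawal, its SAE item is narrower than the Withdrawal rule. If it governs study drug only, both can be applied. On either reading, the Withdrawal section taken alone removes a fully dosed child.

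**5. Possible size at week 12.** The article gives no SAE rate. Assume 0.5% to 2%:
- All arms: 540 × 0.005 = 2.7 to 540 × 0.02 = 10.8 children.
- Per arm: 108 × 0.005 = 0.54 to 108 × 0.02 = 2.16 children.

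Assume also a week-12 cure rate of 72%, borrowed from the praziquantel planning value under Sample size: 0.72 × 108 = 77.76 cured. If the withdrawn children have no week-12 result and are left out of an arm:
- 2 uncured: 77.76/106 = 73.36%, a shift of +1.36 points.
- 2 cured: 75.76/106 = 71.47%, a shift of −0.53 points.
- 1 uncured: 77.76/107 = 72.67%, a shift of +0.67 points.
- 1 cured: 76.76/107 = 71.74%, a shift of −0.26 points.

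**The case against.** **The follow-up texts can be made to work together.** The Adverse events sentence may describe clinical care and the Withdrawal sentence study follow-up. The Withdrawal section refers medically withdrawn children for further care, and the section on risks and compensation covers referral and hospital costs. This is a coherent reading, but the article does not state it, and it still leaves open whether the trial records the final outcome. It does defeat a stronger inference that a reader might draw, namely that children with SAEs lose care. The documents do not support that: the Withdrawal section keeps following these children for the 6 weeks and refers them on.

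**The withdrawal statements are not a plain contradiction.** This stands. A list about study medication that is not presented as complete can coexist with a rule about leaving the study. What remains is ambiguity between the two sections and a poor rule in the second.

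**Primary results are not at risk.** This also stands. It is tempting to argue from safety being part of the primary objective, but under Outcomes the primary safety measure is drug-related adverse events in the first 24 hours. The abstract uses a 6-week horizon. Counting an event does not depend on how long it is then followed, and any SAE in the follow-up period must be reported to the ethics unit within 48 hours. Withdrawn children are sought at week 6, so the primary cure rate is largely protected.

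**Week-12 loss is not certain.** Giving praziquantel after the final visit suggests some later contact, and the section allows for participants who continue with visits. An intention-to-treat analysis and imputation are also planned. None of these, however, commits the trial to a week-12 assessment of a withdrawn child or supplies the stool result.

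**The rewording comes late.** Trial status has recruitment closed on 30 November 2022 and follow-up running until September 2023. For completed visits this is right, and only reporting and outcome retrieval remain.

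**Conclusion.** The point holds, as a minor one. The Adverse events and Withdrawal sections give different end points for SAE follow-up, and the article does not reconcile them, so the handling of an SAE unresolved at day 42 (control) or day 44 (combination arms) is unsettled. The withdrawal rule is in tension with the earlier criteria section, and it is poorly set in its own right because it removes a child for any SAE after dosing has ended and commits to assessment only at week 6.

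The gain from correcting it lies in safety follow-up and week-12 retention. Under assumed SAE rates of 0.5% to 2% and an assumed 72% week-12 cure rate, about 3 to 11 children in all would be withdrawn. Leaving out two from one arm would move that arm's rate by between −0.5 and +1.4 points, mainly in the per-protocol set. Neither assumption comes from trial data, and the shift arises only if those children have no week-12 result. Bias in the week-6 primary comparison should not be inferred.

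**What to change.** In the Withdrawal section, replace the 6-week sentence and the SAE part of the withdrawal sentence with one rule:
- Every SAE is followed to resolution or stabilisation, in line with the Adverse events section.
- An SAE may stop study medication at the clinician's judgement or the guardian's request, without removing the child from the study.
- Both the week-6 and week-12 assessments are sought unless consent is withdrawn.

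The repeated-vomiting clause can stay as it is. For visits already completed, report which rule was applied and obtain the outcome of any SAE left unresolved.

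The cost is a change to two sentences, ethics approval of it where it can still take effect, and a little more safety follow-up. No sample size, margin or analysis method changes.

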### Outcomes

The primary efficacy outcomes are as follows:Cure rate at week 6 after starting study treatments, as assessed by microscopy. The cure rate on each PZQ plus ACT arm is compared with that on the PZQ alone arm.The number of participants with drug-related adverse events in the first 24 h after study treatment.

The secondary outcomes are as follows:Cumulative cure rate at week 12 after enrollment, as assessed by microscopy. The cure rate on each PZQ plus ACT arm is compared with that on the PZQ alone arm.Egg reduction rate at weeks 6 and 12 after starting treatment, as assessed by microscopy and intensity reduction rate, comparing each PZQ plus ACT with PZQ alone arm.The prevalence of re-infection at 12 after starting treatment, as assessed as the number of children who were cured at week 6 follow-up but positive for *S. mansoni* at the week 12 follow-up, compared each PZQ plus ACT arms to the PZQ alone arm.

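### The rule for children who move away sets no time limit, so read literally it drops week-6 cure results already observed and conflicts with the protocol's own analysis sets

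*Protocol article*

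**What the plan says.** All of the text is in the protocol article.

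- **Outcomes:** the primary efficacy outcome is "Cure rate at week 6 after starting study treatments, as assessed by microscopy". Study design places the follow-up visits at weeks 6 and 12.
- **Withdrawal, moving rule:** a child who "moves away from the study area during the study period" is covered by this consequence: "they are considered lost to follow-up and are not included in the efficacy analysis".
- **Withdrawal, next sentence:** it opens with 'However' and says that "data collected up to the time of withdrawal will remain in the study and be used for analysis". It then runs on, after the quoted words, into an unclear clause about whether the participant keeps attending visits.
- **Withdrawal, missed visits:** "Randomized participants who miss one or more scheduled follow-up visits remain in the study and are followed up as planned".
- **Data management and analysis:** "both the per-protocol and intention-to-treat analyses are done, but the per-protocol analysis is the main approach". The per-protocol population is "all participants who were randomized and who completed the study procedures to week 6 or 12".

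**The concern.** The study period runs to week 12, but the primary efficacy outcome is complete at week 6. A child can give the week-6 stool, have it read, and move in week 8. The moving rule takes that child out of the efficacy analysis with no reference to when the move happened.

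There is no statistical reason to discard an observed outcome because of something that happened after it. Doing so makes the week-6 comparison depend, for these children, on where they lived afterwards. The primary denominator would also depend on which sentence the analyst follows. Randomization and blinding states that data analysts are not blinded, so the choice could be made with knowledge of the arm. This is not a detail left to a statistical analysis plan: the protocol states an explicit exclusion, and its own analysis section does not agree with it.

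**Working it through.** **Step 1. One child, each rule in turn.** Take a child who was randomized and treated, whose week-6 stool was read, and who moves in week 8.

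| Rule | Child in the week-6 efficacy analysis? |
|---|---|
| Withdrawal, moving rule | No |
| Withdrawal, 'However' sentence | Yes or not addressed, depending on the reading |
| Data management, per-protocol definition | Yes: procedures completed to week 6 |
| Data management, intention-to-treat analysis | Yes: randomized and treated |
| Withdrawal, missed visits (same child, stays in the area, misses week 12) | Remains in the study |

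The moving rule refers to the efficacy analysis without qualification, so on its face it reaches both the per-protocol and the intention-to-treat analyses. The first and last rows describe children with the same observed data, separated only by the reason for the week-12 absence.

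**Step 2. The 'However' sentence.** It has two readings. If the clause after the quoted words is a slip and was meant to say that data are used regardless of continued attendance, earlier data are kept and the sentence contradicts the exclusion. If it is read as written, it concerns an analysis of continuation and leaves the exclusion untouched. It also refers to withdrawal, whereas the moving rule classes the child as lost to follow-up. Neither reading can be ruled out from the text.

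**Step 3. How many children.** Inputs from Sample size: 102 per arm needed, 5% loss, 108 per arm, 540 in total.

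- The plan's inflation step reproduces: 102 / 0.95 = 107.4, rounded up to 108; 5 × 108 = 540. The 102 is taken as given here.
- Total planned loss: 540 × 0.05 = 27 children, or 27 / 5 = 5.4 per arm.
- Assume that all of this loss is moving away and that half falls after week 6: 13.5 children, or 13.5 / 5 = 2.7 per arm. The documents support neither assumption.

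**Step 4. Effect on an arm's cure rate.** With the planned 72% cure rate, 0.72 × 102 = 73.4, so take 73 cured of 102 (71.6%).

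- One uncured child dropped: 73/101 − 73/102 = +0.7 points.
- One cured child dropped: 72/101 − 73/102 = −0.3 points.
- Three uncured children dropped from this arm and none from the other: 73/99 − 73/102 = +2.2 points.
- The same three dropped from 108 with 78 cured: 78/105 − 78/108 = +2.1 points.

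If moving is unrelated to cure, the chance that three movers are all uncured is 0.28³ = 0.022, about 2%.

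**Step 5. Effect on precision.** The half-width of the 95% CI for the risk difference, with 72% cured in both arms, is 1.96 × √(2 × 0.72 × 0.28 / n). For n = 108 it is 12.0 points; for n = 103 it is 12.3 points. The loss of precision is negligible.

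**The case against.** The strongest reply is that the protocol already says what should happen. The section that defines the analyses includes a child who completed procedures to week 6, and the 'However' sentence, read in sequence, keeps what was collected before the child left. On that view there is one loosely worded sentence in an ethics section and no real exclusion. Part of this stands: a reader might infer that observed outcomes will certainly be thrown away, and the documents do not support that. But an express exclusion remains beside a sentence that does not clearly undo it, and nothing says which section prevails.

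A reader might also infer that the whole week-6 result is conditioned on staying to week 12. It is not. Children who merely miss a visit remain in the study, so only relocation is affected.

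The third reply is about size, and it stands. The 5% covers all loss to follow-up and inflates a sample size built on the cure rate, whose primary time point is week 6. Much of it may therefore concern loss before week 6. The protocol calls moving away unlikely and expects minimal loss, so 2 to 3 children per arm is nearer a ceiling than an estimate. Nothing in the documents links moving after week 6 to arm or to cure, and if there is no such link the expected shift is zero.

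Finally, the rule "Missing data is imputed as either treatment success or treatment failure" sits oddly beside the exclusion, because a child with no stool result could be kept by imputation while a mover with a result is dropped. That rule is about children without a result, however, and this point does not rest on it.

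**Conclusion.** The inconsistency is real and worth correcting. The moving rule, taken literally, removes an observed week-6 outcome because of a later event, and it cannot be reconciled with the per-protocol definition or the intention-to-treat analysis. Whether such data would in fact be lost is unsettled, because the following sentence is garbled.

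The likely effect is small. A shift of about 2 points needs three uncured movers in one arm and none in the comparator, so it is a worst case and should not be read as an expected bias. The figure of 2.7 children per arm rests on the two unsupported assumptions in the working. The case for acting rests on the contradiction and on the discretion it leaves to unblinded analysts.

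**What to change.** Replace the exclusion in Withdrawal with: *A child who moves away contributes every outcome observed before moving; an observed week-6 stool result is always included in the week-6 efficacy analyses, and only later visits are treated as missing.*

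Reword the 'However' sentence to agree, so that it covers moving away as well as withdrawal and states plainly that data already collected are used whether or not the child attends later visits.

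The cost is two sentences, with no extra data and no change to the sample size. The protocol says that changes go to the ethics committee for approval. The rule should be fixed before any analysis of week-6 cure by arm.
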